## 7.10 Duration of Follow Up

Subjects will be followed for 6 month after removal from study or until death, whichever occurs first. Subjects removed from study for unacceptable adverse events will be followed until resolution or stabilization of the adverse event.

## 7.11 Measures to Minimize Bias: Randomization and Blinding

Index participants will be randomized after completion of the social network interview either to the ROBUST intervention or lifestyle intervention, using a random number generator. All index participants, regardless of randomization group, will complete a social network interview to characterize their personal network prior to randomization. The same social network interview will be conducted at 24 weeks. All participants will also receive the same number of coaching sessions, as shown in **Table 1**. They will attend four sessions in person (baseline, week 8, week 16, and week 24), and the remaining 11 sessions will be conducted as a virtual visit. The in-person visits will occur at the Weill Cornell Clinical and Translational Science Center's dedicated research facility. During the in-person sessions, the participant will receive 1:1 dietary counseling with a registered dietician who has been trained on the study protocol. The study research staff complete anthropometric measurements (height, weight, and body composition). Participants randomized to the intervention group will be expected to attend virtual visits at weeks 3, 5, and 15 with their social network member.

Consenting of study participants as well as all study assessments (i.e. baseline, 8 ,16 & 24 weeks) will be conducted by an assessor who is not responsible or involved in the delivery of the coaching sessions, dietary counseling or communication skills sessions. While the study PI & co-investigators will be blinded, the same will not be possible for the trained coach delivering the intervention. Due to budget limitations, having two coaches (i.e. one for the control group and for the intervention group) is not feasible. Since the communication skills training sessions are designed to occur between the index participant and consented social network members, the implication of contamination is reduced as control group participants will not have any consented social network members participating in the study.

*.*

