# 1. Protocol Summary

Full Title: Reducing OBesity Using Social Ties (ROBUST): Randomized Controlled Trial Short Title: ROBUST- RCT

Clinical Phase: III

Principal Investigator: [name], MS

**Study Description:** Randomized controlled trial comparing two behavioral weight-loss interventions; a social-network enhanced lifestyle intervention (Intervention group) and an individual level lifestyle intervention (Control group), among Black and Hispanic adults with obesity over the course of 24 weeks. This study aims to test the feasibility and acceptability reforming interpersonal barriers and addressing social network barriers to behavior change, by engaging social network members in a lifestyle intervention for weight loss compared to the lifestyle intervention alone.

**Sample Size:** *N=* *66 (Intervention index participants)*

*N=132 (Intervention Social Network members)*

*N= 66 (Control participants)*

*N=264 (Total Sample Size)*

**Enrollment:** In the intervention group, this study will enroll 66 index participants and 132 social network member subjects. In the control group, this study will enroll up to 66 index participants.

**Study Population:** Individuals who self-identify as Non-Hispanic Black or Hispanic adults 18 years of age or older with a calculated BMI ≥ 30 kg/m2

**Enrollment Period:** *24 weeks*

**Study Design:** Randomized controlled trial comparing a social-network enhanced lifestyle (intervention group) to an individual-level lifestyle intervention (control group). Subjects in both arms (n=66 each) will receive the same number of behavioral coaching sessions (15 total) with four sessions conducted in person (baseline, week 8, week 16, and week 24), and the remaining 11 sessions conducted virtually. Subjects randomized to the social network intervention will nominate up to a maximum of two members of their social network (n=132) who will also be consented at baseline, complete a brief baseline interview, and attend the virtual coaching sessions with the randomized subject at weeks 3, 5, and 15. The social network members will also complete a close-out study interview at week 24.

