# 4. Subject Selection

## 4.1 Study Population

Subjects that meet the inclusion criteria will be eligible for participation in this study.

Social network subjects identified by index participants that are willing to be engaged in the study will also be eligible for participation in this study.

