## 4.2 Inclusion Criteria Index Participant

1. Black race or Hispanic ethnicity

2. Male or Female 18 years of age or older

3. Calculated BMI > 30kg/m^2^ from objectively measured height and weight by study staff

4. Access & willingness to use program food intake app via home computer or a smartphone

5. Ability to identify at least one adult social network member who will participate in the study

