## 4.4 Inclusion Criteria Social Network Member

1. Male or Female 18 years of age or older
2. Access to the internet or a smartphone

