## 4.5 Exclusion Criteria Social Network Member

1. Speaks a language other than English or Spanish

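### The eligibility criteria do not secure the contamination safeguard in section 7.11: a control participant can be enrolled as an intervention participant's network member, and one household can be split across arms.

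*Protocol*

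**What the plan says.** Section 7.11 explains that the budget allows only one coach for both arms. It then says that the communication skills sessions take place between an index participant and consented network members, and that contamination is reduced because "control group participants will not have any consented social network members participating in the study". Only intervention participants nominate members, up to two each, and those members join the sessions at weeks 3, 5 and 15 (Protocol Summary; section 3.1).

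The Protocol Summary defines the contrast as changing social network barriers "by engaging social network members in a lifestyle intervention for weight loss compared to the lifestyle intervention alone".

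The rules on who may enter are short:

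- Section 4.1, network members: "Social network subjects identified by index participants that are willing to be engaged in the study will also be eligible".
- Section 4.4, member inclusion: "Male or Female 18 years of age or older" and "Access to the internet or a smartphone".
- Section 4.5, the only member exclusion: "Speaks a language other than English or Spanish".
- Section 4.2, item 5, for every index participant before randomisation: "Ability to identify at least one adult social network member who will participate in the study".
- Section 4.3, index exclusions: weight-loss programmes, drugs or surgery; illness or pregnancy; exercise contraindications; food insecurity; language. Nothing on household or network ties.

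**The concern.** The trial tests whether bringing network members into a lifestyle programme adds to the programme alone. That contrast depends on controls not receiving the network component. With one coach for both arms, the protocol's structural argument for this is that controls have no consented members. The argument concerns who is in the study and in which role, so the eligibility criteria would have to enforce it, and they do not.

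The setting makes overlap plausible. Index participants are randomised individually and recruited from four clinics of one institution (section 4.6, recruitment). Item 5 of section 4.2 means that each future control has already identified an adult willing to take part. The scientific rationale (section 3.2) is that influence passes along social ties.

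At stake are the secondary between-arm comparisons and the aim, stated in section 15 under Stopping rules, of obtaining estimates for a larger trial. Overlap would shrink the estimated difference even where power stays high.

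**Working it through.** **Step 1. Test each route of overlap against the criteria.**

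| Route | Barred by 4.1, 4.4 or 4.5? | Barred by 4.2 or 4.3? | What reaches the control |
|---|---|---|---|
| A control is consented as an intervention participant's member | No | No; these govern index entry only | The week 3, 5 and 15 sessions directly, in the supporter's role |
| Two people in one household are index participants in opposite arms | Not applicable | No | Indirect, through the household |
| A person living with a control is consented as someone else's member | No | No | Indirect, through a trained household member |

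The nearest existing rules do not close these routes. The exclusion for active enrolment in a weight-loss programme (4.3) applies to index participants, not to members. Withdrawal for a newly met exclusion (8.2) is at the investigator's discretion. The fidelity review in section 15 deducts points for contamination elements in sampled sessions; it scores what is delivered, not who attends or how attendees are linked.

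**Step 2. Reproduce the plan's power.** Inputs from section 15, Stopping rules: 132 participants, 15% attrition, 8 lb difference, SD 10.4. From section 3.1: even randomisation, so 66 per arm. Assumed, because no level is stated: two-sided alpha 0.05.

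Analysed per arm: 66 × 0.85 = 56.1, taken as 56. By the normal approximation:

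- standard error = 10.4 × √(2/56) = 1.965 lb
- 8 / 1.965 = 4.07
- power = Φ(4.07 − 1.96) = Φ(2.11) ≈ 98%

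The noncentral t gives 98.1%, against 98% in the plan. For 30%, 40% and 50% dropout it gives 95.4%, 91.8% and 86.8%, against 96%, 92% and 88% in the plan's table. The plan's figures reproduce.

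**Step 3. Illustrate dilution.** Let a share c of controls receive the full effect, with the SD unchanged. The expected difference becomes 8 × (1 − c). The documents give no c, so a range is shown (noncentral t).

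| c | About how many of 56 controls | Difference (lb) | Power, 56 per arm |
|---|---|---|---|
| 0 | 0 | 8.0 | 98% |
| 5% | 3 | 7.6 | 97% |
| 10% | 6 | 7.2 | 95% |
| 20% | 11 | 6.4 | 90% |
| 30% | 17 | 5.6 | 81% |

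At the plan's high-alert dropout of 50% (33 per arm), power is 87% at c = 0, 79% at 10% and 69% at 20%. These values stack two adverse assumptions.

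Full-effect transfer is an upper-end assumption. If an exposed control gained only half the effect, c = 10% would act like c = 5%.

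**The case against.** The case against has four parts.

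First, the sentence in 7.11 answers the shared-coach problem. It claims only that contamination is reduced, and since controls nominate nobody it is true of a control's own nominees. This stands. A reader might infer that the safeguard fails outright; the text supports only that it is not guaranteed.

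Second, a tie does not by itself deliver the intervention. Appendix B builds the sessions around one index participant and that person's members, who set a supportive goal together. A control who attends as a member attends as the supporter, and the control's own network stays untrained. A control's spouse who supports someone else gives the control no session. This also stands: only the control-as-member route exposes a control directly, and even that is not the full intervention. A reader who treats every tie as full delivery goes beyond the documents.

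Third, no overlap rate is given, and at planned attrition about 6 of 56 controls would need the full effect before power fell to 95%. This stands against using the power figures as evidence of harm. It does not remove the gap.

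Fourth, other measures exist: fidelity scoring, and network interviews of all index participants at baseline and week 24. These could help detect contamination, but none prevents it. How correlated outcomes of linked participants would be modelled is commonly left to the statistical analysis plan, which is not at hand, so that is not held against the protocol.

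**Conclusion.** The point holds in a limited form. The eligibility criteria allow a control to become a consented network member and allow one household to be split across arms, so the safeguard in 7.11 rests on chance rather than on a rule. Overlap would bias the secondary between-arm comparisons toward no difference, in proportion to the share of controls exposed and the part of the effect that reaches them. On the full-effect assumption, with two-sided alpha 0.05, 10% exposure costs 0.8 lb and about 3 points of power at planned attrition.

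Two stronger readings are not supported. The stated 98% power is not shown to be wrong: it reproduces, and no document gives an exposure rate. Nor are the primary conclusions undermined: the primary endpoints are thresholds for attendance, member engagement and completion (section 1.2.4), which contamination of controls largely leaves alone.

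**What to change.** - **Section 4.5:** add that a network member may not be a current or past index participant in this trial and may not live with a control index participant.
- **Section 4.3:** add that an index participant may not live with an enrolled index participant and may not already be a consented network member of one.
- **Check:** compare against the enrolment list at screening and again at nomination. Ask the household question directly, because the protocol does not say that the network interview stores identifiable contacts. The control-household check uses allocation, so it should be done by someone other than the investigators whom 7.11 describes as blinded.
- **Record:** log any overlap found later. This would also catch the reverse order, where a member is consented first and a person living with that member later enrols and becomes a control.
- **Leave alone:** do not bar two intervention participants from sharing a member. That contaminates no control.

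The cost is one added line in each of two sections, a household question and a look-up. A few otherwise eligible people or nominees would be turned away. Because nomination follows randomisation, refused nominees could slightly lower the result for the 80% member-engagement endpoint unless the participant may name a replacement; the protocol should allow that.

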## 7.12 Study Intervention/Follow-up Compliance

Adherence to the protocol will be assessed and verified through the completion of REDCap forms each time that a study team member speaks with participants. This REDCap form will contain questions to verify the date of each coaching session and verify the collection of any related materials (i.e. verify collection of food logs, etc). It is mandatory for study team members to complete the REDCap form and the phone log form as these documents will be used to calculate study intervention compliance.

5 attempts will be made to get participants to return for study follow up appointments via text and calls to the participant. A participant will be considered “lost to follow up” when 3 consecutive sessions have been missed and the study team can no longer get in contact with the participant. Participants that are not lost to follow up will be considered as no longer participating in the study when week 24 of the study (close out interview) has been completed.

# 8. Study Intervention Discontinuation and Participant Discontinuation/Withdrawal

## 8.1 Discontinuation of Study Intervention

Criteria for discontinuing the study intervention is as follows:

- Cardiovascular, pulmonary, hypoglycemia: Adverse events will be defined as cardiovascular (MI, CVA, death), acute shortness of breath, or hypoglycemia precipitated by changes in dietary intake or the physical activity chosen for the study requiring hospitalization/emergency room visit or a physician office visit. Non-routine office visits for cardiac or pulmonary disease or diabetes are expected and not serious unless they lead to the above events.
- Major depressive episode or anxiety attack: Infrequent likelihood. A participant may become depressed, anxious or severely embarrassed if friends/family/acquaintances find out that the person is participating in and/or not losing weight in the program. Patients have the option of not answering any questions they do not want to. As this is a voluntary study, a participant is free to withdraw from the study at any point if they feel uncomfortable or do not want to continue.
- Medication Side Effects: Infrequent risks. The study does not prescribe medication. Weight loss can cause a change in the dose of medication needed to treat common health conditions such as hypertension, diabetes and thyroid dysfunction. Participants will be required to communicate their participation in the study along with their weight loss to a primary care physician.
- Musculoskeletal: Musculoskeletal injury due to the physical activity chosen for this study resulting in hospitalizations, emergency department visits, or treatment for fracture in any setting will be considered expected serious adverse events. Non-routine office visits for musculoskeletal injury are expected and not serious unless lead to the above events. Temporary minor incapacitation due to muscle soreness is also expected and not serious.

Discontinuation from the social network intervention does not mean discontinuation from the study, and remaining study procedures should be completed as indicated by the study protocol. If a clinically significant finding is identified (including, but not limited to changes from baseline) after enrollment, the investigator or qualified designee will determine if any change in participant management is needed. Any new clinically relevant finding will be reported as an adverse event (AE).

The data to be collected at the time of study intervention discontinuation will include the following:

- Adverse event form
- If applicable, withdrawal form

## 8.2 Participant Discontinuation/Withdrawal from the Study

Participants are free to withdraw from participation in the study at any time upon request.

An investigator may discontinue or withdraw a participant from the study for the following reasons:

- Pregnancy
- Significant study intervention non-compliance
- If any clinical adverse event (AE), laboratory abnormality, or other medical condition or situation occurs such that continued participation in the study would not be in the best interest of the participant
- Disease progression which requires discontinuation of the study intervention
- If the participant meets an exclusion criterion (either newly developed or not previously recognized) that precludes further study participation
- Participant lost to follow-up after several attempts to contact subject to schedule study visit.

The reason for participant discontinuation or withdrawal from the study will be recorded on the Withdrawal Case Report Form (CRF). Subjects who sign the informed consent form and are randomized but do not receive the study intervention will be replaced. Subjects who sign the informed consent form, and are randomized and receive the study intervention, and subsequently withdraw, or are withdrawn or discontinued from the study, will not be replaced.

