## 12.1 Study Design/Endpoints

This randomized controlled trial will use the following primary endpoints as the promising range to justify further testing of this agent:

- At least 75% attendance rate for the participant and their network members in their respective behavioral coaching sessions.
- 80% of participants or more to have at least one network member engage in the study.
- 85% of participants and their network members or more to complete the final study assessment.

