## Measurement and reporting of participant compliance to treatment protocol:

Session attendance will be measured as a marker of adherence, with a benchmark of attending at least 75% of the coaching/assessment sessions for both index participants (11 out of 14) and social network members (3 out of 4). 'Treatment (intervention) fidelity' will be assessed in three ways. The first is a checklist in REDCAP that the coach will complete at the end of each session. This checklist will also serve as a reminder to the coach about the active ingredients to be delivered during the session. The second method is a monthly review of a random sampling of 10% of the coaching sessions. Points will be given for each required treatment element delivered correctly and subtracted for any contamination elements. If the average fidelity falls below 90%, the coach will be retrained. The third is by each tracking the session duration in minutes. The coach will assess enactment fidelity at the beginning of each coaching session using a simple yes/no checklist. This data will be reviewed in bi-weekly team meetings (study coordinator, PI and interventionists) and reviewed by the safety officer bi-annually. If the safety officer has concerns about whether intervention fidelity has reached a level that might inhibit the ability of the study to test its primary hypotheses, she will suggest a conference call for study investigators to discuss methods for improving study adherence.

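### Section 8.2 lets staff withdraw participants from the study for undefined non-compliance, although attendance and week-24 completion are primary endpoints

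*Protocol*

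**What the plan says.** Section 8.2 introduces its list with "An investigator may discontinue or withdraw a participant from the study for the following reasons", and one entry is "Significant study intervention non-compliance". Neither that section nor any other says what counts as significant. People withdrawn after receiving the intervention are not replaced.

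Section 12.1 sets three primary endpoints. The first concerns attendance: "At least 75% attendance rate for the participant and their network members in their respective behavioral coaching sessions". The second concerns engagement, with a target that four in five participants bring in a network member. The third concerns completion: "85% of participants and their network members or more to complete the final study assessment".

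Compliance and attendance rest on the same records. Section 7.12 requires staff to complete a REDCap form that verifies the date of each coaching session, plus a phone log, and adds that "these documents will be used to calculate study intervention compliance". The compliance part of the data and safety monitoring plan (section 15) says "Session attendance will be measured as a marker of adherence, with a benchmark of attending at least 75% of the coaching/assessment sessions". It gives this as 11 of 14 for index participants and 3 of 4 for network members.

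Two other sections point away from 8.2. Section 8.1 states that "Discontinuation from the social network intervention does not mean discontinuation from the study" and expects the remaining procedures to be carried out. Section 7.9 lists the events that end follow-up, and non-compliance is not among them.

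**The concern.** In a feasibility trial, poor attendance is a result to be measured. Section 8.2 also makes it a permitted reason to stop measuring. Two things are at stake.

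First, part of the completion endpoint can reflect how strictly staff apply an undefined criterion, when it is meant to show whether participants stay.

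Second, the people removed would be the least adherent, so their missing week-24 weights would not be missing at random with respect to the weight comparison. An analysis plan can fix denominators and missing-data methods afterwards. It cannot bring back an assessment that was never made because a reachable person had been withdrawn.

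**Working it through.** **The protocol's only power figure.** The feasibility targets carry no sample size calculation. The one power statement (section 15, stopping rules) concerns weight: 132 participants, 15% attrition, a difference of 8 lb, SD 10.4, power 98%. Significance level and sidedness are not stated, so I assume two-sided 0.05.
- n per arm = 132 × 0.85 / 2 ≈ 56
- 8 / (10.4 × √(2/56)) = 4.07, and 4.07 − 1.96 = 2.11, so power = 98.3% (98.1% with the t distribution)

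The figure reproduces, and so do the tabulated 96%, 92% and 88% at 30%, 40% and 50% dropout. The calculation treats dropouts only as fewer participants. It says nothing about who drops out, and the present point does not depend on it.

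**Completion.** Section 12.4.1 defines retention as week-24 completers among those who completed baseline, so a withdrawn participant stays in the denominator as a failure. I count index participants only, all with a baseline assessment.
- Intervention arm: 0.85 × 66 = 56.1, so 57 must complete and at most 9 may not.
- Both arms: 0.85 × 132 = 112.2, so 113 must complete and at most 19 may not.
- The 15% attrition that section 15 expects is 0.15 × 66 = 9.9 and 0.15 × 132 = 19.8, so the plan's own forecast leaves no slack.

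The number of staff withdrawals that turns a pass into a miss, if each person withdrawn would otherwise have attended week 24, is (completers without withdrawals) − (completers required) + 1:

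| Assumed completion without such withdrawals | Of 66 | Withdrawals to miss | Of 132 | Withdrawals to miss |
|---|---|---|---|---|
| 88% | 58 | 2 | 116 | 4 |
| 90% | 59 | 3 | 119 | 7 |
| 92% | 61 | 5 | 121 | 9 |
| 95% | 63 | 7 | 125 | 13 |

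For example, 59 − 3 = 56 and 56/66 = 84.8%; 119 − 7 = 112 and 112/132 = 84.8%.

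**Attendance.** Section 12.4.1 takes the proportion of sessions attended over the 24 weeks but does not say how sessions after an investigator's withdrawal count. As an illustration, suppose good attenders come to 80% of sessions, and 15% of participants are poor attenders who would come to 30%.
- Nobody withdrawn: 0.85 × 0.80 + 0.15 × 0.30 = 72.5%
- Poor attenders withdrawn after 2 sessions, counted over 14: 0.85 × 0.80 + 0.15 × 2/14 = 70.1%
- Poor attenders withdrawn and dropped from the denominator: 80.0%

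With 5% to 20% poor attenders the three values run from 77.5% to 70.0%, from 76.7% to 66.9%, and stay at 80.0%. Withdrawal can therefore lower or raise the rate, depending on a denominator that the protocol leaves open.

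**The case against.** The case against has force on several points.

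- **The power is discretionary.** Nothing removes a poor attender automatically, and the protocol otherwise works to keep people: five contact attempts in section 7.12, prompt rescheduling and counselling in section 8.3. This stands; poor attendance permits removal but does not trigger it.
- **Unreachable people are lost anyway.** Those who miss three sessions and cannot be contacted are already lost to follow-up. This stands too. The clause matters only for reachable poor attenders who would have come at week 24.
- **The completion effect is conservative.** Withdrawn people count as failures, so it cannot create a false success. That is true, but a false failure also misinforms the decision on a larger trial.
- **Follow-up may continue after removal.** Section 7.10 provides six months of follow-up after removal, and section 7.9 does not end follow-up for non-compliance. This is the best reply. However, section 7.10 names no assessment, Table 1 schedules none for withdrawn people, and section 3.4 ends the study at completion of the withdrawal procedure. The sections need reconciling before the reply can be relied on.
- **Section 8.1 does not squarely contradict 8.2.** Its sentence follows a list of adverse-event criteria. This is correct; the two sit badly together without being opposites.

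A reader might also infer four stronger things that the text does not support.

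1. *The clause inflates attendance past 75%.* With 59 people at 80% and 7 at 30%, the rate is (47.2 + 2.1)/66 = 74.7%, and 80% once the seven are excluded. No section excludes them, and the fixed counts in section 15 point the other way. With six poor attenders the rate is (48.0 + 1.8)/66 = 75.5%, a pass either way.
2. *An unblinded coach controls removal.* Section 7.12 assigns the compliance forms to study team members generally, section 8.2 gives the decision to an investigator, and section 7.11 says the principal investigator and co-investigators are blinded.
3. *The analysis ceases to be by intention to treat.* Section 12.4.2 specifies a modified intention-to-treat analysis, and section 12.6.2 includes anyone with a coaching session after randomization. A later withdrawal costs data, not membership of the analysis set.
4. *All three primary endpoints are affected.* Network-member engagement is not shown to be.

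**Conclusion.** The point holds in a limited form. An undefined, discretionary ground for withdrawal from the study overlaps with the behavior that two of the three primary endpoints measure. For completion the direction is clear and the margin small: 2 to 7 such withdrawals among 66, or 4 to 13 among 132, turn a true completion rate of 88% to 95% into a miss of the 85% target. This assumes that withdrawal from the study ends assessments and that each person withdrawn would otherwise have attended week 24. How often the clause would be used is unknown. For weight, the result is adherence-related missing data in a comparison meant to follow intention-to-treat principles. For attendance, the direction cannot be determined from the protocol.

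**What to change.** - Remove non-compliance from the section 8.2 reasons for withdrawal from the study, and reconcile that section with sections 7.9 and 8.1. Align sections 3.4 and 7.10 with the result.
- State that participants who stop attending remain enrolled and are invited to the week-24 assessment unless they withdraw consent or cannot be reached.
- State that attendance is counted over all scheduled sessions for everyone randomized, and name the session total. The protocol summary gives 15, while the section 15 benchmark uses 14.

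This concerns outcome collection only; withdrawal on safety grounds is not affected. The cost is one deleted line, a few clarifying sentences, a few more week-24 contacts, and possibly a slightly lower reported attendance rate.
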